### Sample size, power and statistical methods

Non-inferiority of oral flucloxacillin and placebo relative to oral flucloxacillin and phenoxymethylpenicillin for the above primary and secondary outcomes will be assessed. Sample size per treatment arm is calculated according to an assumed treatment success rate of 85% with oral flucloxacillin and phenoxymethylpenicillin, an equivalence threshold Δ = 12.5% and an α = 0.025 (as this is a non-inferiority study). Sample sizes were calculated using PASS statistical software (Hintze J.(2008) PASS 2008. NCSS, LLC, Kaysville, Utah, USA http://www.ncss.com). Given the preferred study power of 90% for non-inferiority trials, a minimum sample size of 172 in each treatment group is required (n = 344). Non-inferiority will be assessed using a one-sided confidence interval (CI) on the difference of proportions between the two groups. If the upper limit of the CI is less than the equivalence threshold of 12.5%, then non-inferiority is inferred.

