##### Secondary outcomes

•Clinical failure: a failure of the initial maximal diameter of infection to reduce by ≥50%

•Clinical relapse: initial improvement in cellulitis at the EOT visit followed by a worsening or re-appearance of cellulitis at the TOC visit.

•Quality of life: the SF-36 and the ESTI score at the EOT visit will be measured.

•Compliance with therapy: the number of unused study medications counted at the EOT visit will be measured.

•Adverse Events: all adverse events will be recorded and submitted to the Irish Medicines Board and the Research and Ethics Committee.

•Microbiological profile: the results of specimens sent for culture to receiving laboratories will be profiled.

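### Non-inferiority is promised for every secondary outcome, but the only margin and rule given were set for the primary cure proportion

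*Protocol article*

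**What the plan says.** The section Sample size, power and statistical methods opens with a commitment covering all outcomes: "Non-inferiority of oral flucloxacillin and placebo relative to oral flucloxacillin and phenoxymethylpenicillin for the above primary and secondary outcomes will be assessed". The rest of the section describes one test. The method is a "one-sided confidence interval (CI) on the difference of proportions between the two groups", and the decision rule is: "If the upper limit of the CI is less than the equivalence threshold of 12.5%, then non-inferiority is inferred". The margin stands beside an assumed 85% success rate on dual therapy, "an α = 0.025 (as this is a non-inferiority study"), 90% power and 172 patients per arm. The order of subtraction is not stated, and no other margin appears in the article. Data analysis adds that both the intention-to-treat and the per-protocol results must exclude the margin.

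Secondary outcomes lists six items: clinical failure (the complement of the primary outcome), clinical relapse, quality of life, compliance, adverse events and microbiological profile. Relapse is defined as "initial improvement in cellulitis at the EOT visit followed by a worsening or re-appearance of cellulitis at the TOC visit". For quality of life the text is "Quality of life: the SF-36 and the ESTI score at the EOT visit will be measured". Compliance is a count of unused medication, and microbiology is a profile of culture results.

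**The concern.** A non-inferiority conclusion needs a margin on the scale of the outcome and a stated direction of harm. Here the conclusion is promised for outcomes of several kinds, and the only margin is 12.5 points on a proportion, chosen next to an 85% success rate. Two problems follow.

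- For scores, counts and a culture profile, a 12.5-point difference in proportions has no meaning. The promised assessment cannot be carried out as written.
- For relapse and adverse events the rule can be computed. If these events are uncommon, though, 12.5 points is large compared with the event rate itself, and monotherapy could be called non-inferior on relapse or safety although its event rate had doubled or tripled.

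At stake are the secondary claims in the trial report. The primary conclusion is not.

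**Working it through.** **1. The plan's own figure.** Inputs from Sample size, power and statistical methods: success 0.85 in the dual arm, margin 0.125, one-sided α 0.025 (z = 1.960), power 0.90 (z = 1.282). Equal true success in both arms is assumed.

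n per arm = 2 × 0.85 × 0.15 × (1.960 + 1.282)² / 0.125² = 171.48, rounded up to 172. The stated 172 per arm reproduces.

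**2. The primary rule.** I enumerated two independent binomials exactly, with 172 per arm and an unpooled Wald upper limit at one-sided 0.025. Non-inferiority is declared if that limit is below 0.125. With the difference taken as cure on dual minus cure on monotherapy:

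| True cure, dual vs mono | Declared non-inferior |
|---|---|
| 85% vs 85% | 90.1% |
| 85% vs 72.5% (at the margin) | 2.6% |

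These match the planned power and α. Clinical failure taken as monotherapy minus dual gives the identical decision, with 2.6% at 15% versus 27.5%.

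**3. Which secondary outcomes the rule can reach.**

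| Outcome | Form in the article | Does the rule apply? |
|---|---|---|
| Clinical failure | complement of cure | yes, same decision as the primary |
| Relapse | binary | computable, but no rate or margin of its own |
| Adverse events | recorded events | computable only as a proportion with an event; no rate or margin of its own |
| SF-36, ESTI | scores | no |
| Compliance | count of unused medication | no |
| Microbiology | descriptive profile | no |

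**4. The rule applied to relapse, with the direction correct (monotherapy minus dual).** The article gives no relapse rate, so all rates below are assumptions. The same enumeration is run for two denominators. The first is all 172 per arm. The second is those who improved and can therefore relapse; if improvement is equated with the assumed 85% cure, that is 0.85 × 172 = 146 per arm.

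| True relapse, dual vs mono | Difference | Non-inferior, 172 per arm | Non-inferior, 146 per arm |
|---|---|---|---|
| 2% vs 6% | 4 points | 96% | 93% |
| 5% vs 10% | 5 points | 74% | 68% |
| 10% vs 15% | 5 points | 56% | 50% |
| 5% vs 15% | 10 points | 13% | 12% |
| 5% vs 17.5% (at the margin) | 12.5 points | 3% | 3% |

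Rough check of the second row at 172 per arm: SE = √(0.10 × 0.90/172 + 0.05 × 0.95/172) = 0.0283, and Φ((0.125 − 0.05)/0.0283 − 1.96) is about 0.76, close to the exact 0.74.

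The test does what a 12.5-point margin asks of it. The question is whether that margin was ever meant for an outcome this rare, and the article gives no reason to think so.

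**The case against.** The article does not say that the 12.5-point rule decides each secondary outcome. Only the opening sentence names those outcomes. The rule appears in the sample-size context and is limited to proportions, and Secondary outcomes speaks only of measuring, recording or profiling most of the items. An analysis plan is to be agreed before unblinding and could carry separate methods. The relapse figures rest on assumed rates, and the first three scenarios lie inside the stated margin, so frequent passing is expected. Whether 12.5 points is too loose for relapse is partly a clinical judgement.

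Much of this stands, and it keeps the point minor. What it does not remove is the commitment itself: the opening sentence promises a non-inferiority assessment of every listed outcome, and the article offers no other rule for making one.

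Two stronger readings are tempting, and the text supports neither.

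- **A reader might infer that the primary test runs backwards, because the subtraction order is missing.** Taken as monotherapy minus dual, the rule would indeed pass a true fall in cure from 85% to 72.5% in 99.99% of trials. But an upper limit compared with +12.5 points, the stated aim of showing monotherapy non-inferior, and the 172 per arm fit only dual minus monotherapy. Nor does the article impose one arithmetic order on every outcome, so cure and failure need not conflict.
- **A reader might infer that the plan would produce false claims across the secondary outcomes.** For scores, counts and cultures the rule gives no decision, rather than a false one. For relapse and adverse events it could support a weak claim if someone chose to apply it.

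**Conclusion.** The point holds, at minor severity. Non-inferiority is promised for outcomes that have no usable margin: the one rule supplied is undefined for SF-36, ESTI, unused-tablet counts and cultures, and may be loose for relapse and adverse events. The size of that looseness depends on event rates that the article does not give. Under the assumed relapse rates, a tripling from 2% to 6% passes in 93% to 96% of trials, a doubling from 5% to 10% in 68% to 74%, and a rise from 10% to 15% in 50% to 56%, depending on the denominator. These figures also assume an unpooled Wald limit and complete data. The primary comparison and the sample size are unaffected. Reporting clinical failure beside cure is redundant but harmless, and it need not be dropped.

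**What to change.** Revise the opening and closing sentences of Sample size, power and statistical methods along these lines:

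- The formal non-inferiority conclusion is drawn for the primary outcome only.
- The difference is the cure proportion on dual therapy minus the cure proportion on flucloxacillin alone. Non-inferiority is concluded if the upper limit of the one-sided 97.5% confidence interval (the same as the upper limit of the two-sided 95% interval) is below 12.5 points in both the intention-to-treat and the per-protocol analysis.
- Secondary outcomes are reported as estimates with two-sided 95% confidence intervals and no non-inferiority conclusion, unless an outcome is given its own justified margin and direction beforehand.

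The cost is wording, plus the loss of secondary non-inferiority claims. No patients are added and 172 per arm stands. Trial status says that funding is still needed before enrolment can begin, so the change can be made before any data exist.

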### Patient randomisation

The randomisation process has been designed by CSTAR (Health Research Board Centre for Support and Training in Analysis and Research), Dublin, Ireland. Trial randomisation codes will be generated by CSTAR. It is intended to use block randomization using a permuted block design with a computer random number generator without stratification, to create two treatment groups of 172 patients (n = 344).

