### Study procedure

#### Interventions

##### Wound/skin care

Standard wound care for cellulitis will be permissible in both groups and may include saline soaks and non-adherent dressings. The area of infection will be drawn with a waterproof skin marker and the maximal diameter of the area of infection measured and recorded.

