#### Bias and confounding variables

In terms of selection bias, we feel that this study targets a patient population to whom this research ultimately will be clinically applicable and valuable. Every effort will be made to ensure that recruitment of participants occurs over all 24-hour periods (including weekends) by having patients recruited by the ED physician treating the patient. We anticipate that the randomised, double-blinded, controlled design of this study will minimise the effect of confounding variables on our analysis.

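### The primary non-inferiority interval uses no covariate; adjusting it for the recorded enrolment lesion diameter could add modest precision at almost no cost

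*Protocol article*

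**What the plan says.** The protocol article, under 'Sample size, power and statistical methods', gives the decision rule: "Non-inferiority will be assessed using a one-sided confidence interval (CI) on the difference of proportions between the two groups". Non-inferiority follows if the upper limit lies below 12.5 percentage points. The sample size rests on "an assumed treatment success rate of 85% with oral flucloxacillin and phenoxymethylpenicillin", one-sided alpha 0.025 and 90% power, giving 172 per arm. No model or covariate is mentioned. 'Data analysis' requires both the intention-to-treat and the per-protocol analysis to exclude the margin.

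Three other sections bear on the point:

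- 'Wound/skin care' has the lesion outlined and "the maximal diameter of the area of infection measured and recorded". 'Primary outcome' and 'Measurement of the primary outcome' use the enrolment measurement as the reference for the 50% reduction that defines cure.
- 'Patient randomisation' specifies "block randomization using a permuted block design with a computer random number generator without stratification".
- 'Bias and confounding variables' relies on randomisation and blinding, expecting that the "controlled design of this study will minimise the effect of confounding variables on our analysis".

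'Following completion of the study' refers to a statistical analysis plan to be agreed before unblinding. That plan is not shown.

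**The concern.** The trial's conclusion depends on whether one confidence limit clears a fixed margin, in two analysis sets. If a baseline variable predicts the outcome, an analysis that leaves it out has a wider interval than it needs. Its point estimate also carries whatever imbalance in that variable arose by chance.

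Enrolment diameter is the natural candidate. It must be known for every evaluable patient, because cure cannot be determined without it. Expressing the outcome as a percentage reduction removes the influence of baseline size only if small and large lesions are equally likely to halve within 7 to 10 days. Nothing in the protocol establishes that they are. If they are not, the planned interval gives up some precision that the trial's own data could supply.

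**Working it through.** **Inputs from the protocol.** Success 85% with dual therapy; margin 0.125; one-sided alpha 0.025; power 90%; 1:1 allocation; 172 per arm. Equal true success in both arms is assumed, as is usual for such a calculation.

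**1. Reproduce the plan's figure.** With an unpooled variance,

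n = 2 × 0.85 × 0.15 × (1.960 + 1.282)² / 0.125² = 0.255 × 10.507 / 0.015625 = 171.5, rounded up to 172.

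At 172 per arm, SE = √(0.255/172) = 0.0385. Power = Φ(0.125/0.0385 − 1.960) = Φ(1.286) = 90.1%. The interval half-width is 1.960 × 0.0385 = 7.55 points. The stated sample size is therefore exactly that of an unadjusted comparison of two proportions.

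**2. Effect of adjustment.** If enrolment diameter explains a share R² of the outcome variance, the adjusted risk difference has SE = √(0.255 × (1 − R²)/172). The protocol gives no R². I took a logistic model with a normally distributed (standardised) covariate, marginal success 85% and an assumed odds ratio per standard deviation (SD), from which R² follows.

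| Assumed odds ratio per SD | R² | Power at 172 per arm | Half-width (points) | n per arm for 90% power |
|---|---|---|---|---|
| 1 (no association) | 0 | 90.1% | 7.55 | 172 |
| 1.5 | 2.1% | 90.7% | 7.47 | 168 |
| 2 | 5.9% | 91.7% | 7.32 | 162 |
| 3 | 13.6% | 93.7% | 7.01 | 149 |

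For example, at odds ratio 2: SE = 0.0385 × √(1 − 0.0594) = 0.0373, and Φ(0.125/0.0373 − 1.960) = 91.7%.

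**3. Effect of chance imbalance.** With 172 per arm, the SE of the between-arm difference in mean diameter is √(2/172) = 0.108 SD. Under the same logistic models, the average change in cure probability per SD of diameter is 0.0506, 0.0831 and 0.121 at odds ratios 1.5, 2 and 3. An imbalance of 1.96 SE shifts the unadjusted difference by 1.96 × 0.1078 × slope:

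- odds ratio 1.5: 0.2113 × 0.0506 = 1.1 points
- odds ratio 2: 0.2113 × 0.0831 = 1.8 points
- odds ratio 3: 0.2113 × 0.121 = 2.6 points

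**4. Simulation check.** With 10,000 trials per setting, the unadjusted test had 89.9% to 90.4% power and a one-sided type I error of 2.3% to 2.7% at every strength tried. A regression-adjusted risk difference with robust SE had 89.9%, 90.4%, 91.5% and 93.1% power at odds ratios 1, 1.5, 2 and 3, with type I error of 2.4% to 2.7%. A separate simulation of logistic standardisation (3,000 trials per setting) agrees. Unadjusted against adjusted power was 90.8% and 90.9% with no association, 90.5% and 92.5% at a correlation of 0.26, and 90.0% and 93.4% at 0.34.

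**The case against.** The strongest reply is that nothing in the stated test is wrong. It is a standard non-inferiority analysis, it matches the sample-size calculation, and it meets the 90% target. Its confidence interval already allows for chance imbalance across repeated randomisations. The protocol never calls the interval unadjusted, and a standardised risk difference is also a difference of proportions, so the unseen analysis plan could add the covariate. All of this stands, and it limits the point to an improvement. It does not remove the point. The article already fixes the test and its pass/fail rule, names no covariate, and sizes the trial for the unadjusted version.

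Four stronger readings are tempting, and the protocol supports none of them:

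- *That the plan takes no account of lesion size.* Cure is defined relative to the enrolment diameter, so size is already partly scaled out. What is open is whether it still predicts reaching the threshold.
- *That the primary result would be biased or the trial underpowered.* Steps 1 and 4 show the planned power and close to nominal type I error without adjustment.
- *That the missing stratification is the cause.* Stratifying by another factor, such as site, would not balance lesion size, and model adjustment works without stratification.
- *That the gain is large.* A correlation of 0.5 between diameter and cure would cut the variance by 25% and lift power to 96.3%, but the protocol gives no basis for that value. Under the logistic model it needs an odds ratio of about 8 to 9 per SD. At 8, cure would be about 99% one SD to the favourable side, 68% one SD to the unfavourable side and 21% at two SD. That is very strong for an outcome already scaled to baseline.

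**Conclusion.** The point holds as a modest efficiency improvement, not as correction of an error. The gain is about 0.6, 1.6 and 3.6 power points at assumed odds ratios of 1.5, 2 and 3 per SD (90.7, 91.7 and 93.7 minus 90.1). The last two equal 20 and 46 fewer patients in total at the planned power (344 − 2 × 162 and 344 − 2 × 149). With no association, power is essentially unchanged.

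The size depends on the prognostic strength of diameter, which the protocol does not give, and on a normally distributed covariate in a logistic model. That the primary interval carries no covariate is read from the article alone; the analysis plan might add one. The case for the change is the asymmetry: some benefit if diameter is prognostic, and almost no cost if it is not.

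**What to change.** Before unblinding, pre-specify the primary analysis as a covariate-standardised risk difference:

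- Fit one logistic model of cure on treatment and log enrolment diameter.
- Average the predicted cure probabilities under each treatment over all patients in the analysis set.
- Take the difference, with a robust (influence-function or bootstrap) confidence interval.
- Apply this in both the intention-to-treat and the per-protocol set, against the same 12.5-point margin at one-sided alpha 0.025.
- Report the unadjusted difference and its interval as a sensitivity analysis.

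The effect measure, margin, alpha and 172 per arm are unchanged. The cost is one sentence in the statistical methods and a few lines of code, with no new data, visits or patients. The primary result becomes slightly less simple to present. 'Trial status' says further funding is needed before enrolment can start, so there is time to specify this.

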#### Data analysis

Both intention-to-treat (ITT) and per-protocol analysis will be performed. ITT analyses include all patients randomised to the trial regardless of whether they satisfied entry requirements, received the assigned treatments, withdrew from the trial or adhered to the protocol. Missing values will be imputed using a suitable imputation method (last value carried forward or mixed model). A per-protocol analysis includes only patients who completed the full course of treatment and adhered to the protocol requirements. In a non-inferiority trial setting a per-protocol analysis may be more appropriate since it is more likely to reflect actual differences between the two treatments. Furthermore, ITT analysis may be interpreted as being too liberal in a non-inferiority trial and may bias toward making the two treatments appear similar
[24]. As a result, both an ITT and per-protocol analysis will be performed on the resulting data to assess non-inferiority of the placebo/flucloxacillin combination. In particular, to declare non-inferiority, both ITT and per protocol analysis should exclude the non-inferiority margin.

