##### Follow-up

Patients will be telephoned at 3 to 5 days by a study investigator to encourage treatment compliance and EOT visit follow-up. Any deterioration in patient symptoms may be addressed at this visit and a return for clinical assessment may be recommended. The patient will be reviewed at 7 to 10 days after treatment commencement (EOT visit) in the enrolment centre and the area of infection will be measured. At this visit, the patient will be given an SF-36 and ESTI score to complete. A final TOC visit or telephone call will be arranged for 30 days after the enrolment of the patient into the trial.

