#### Outcome measures

##### Primary outcome

The primary outcome measure under study is the proportion of patients treated in each group in which there is greater than or equal to a 50% reduction in the maximal diameter of erythema from the area measured at enrolment to that at the end-of-treatment visit (7 to 10 days).

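### Last value carried forward would normally score a patient with no end-of-treatment measurement as a failure, which costs power and weakens the ITT check

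*Protocol article*

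**What the plan says.** Under Data analysis, the ITT set is everyone randomised, including those who withdraw, and gaps are handled thus: "Missing values will be imputed using a suitable imputation method (last value carried forward or mixed model". No choice is made between the two methods. The same section warns that "ITT analysis may be interpreted as being too liberal in a non-inferiority trial", and therefore requires both the ITT and the per-protocol analysis to exclude the margin before non-inferiority is declared.

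The measurement schedule is spread over three sections:

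- Enrolment (Wound/skin care): "the maximal diameter of the area of infection measured and recorded".
- Day 3 to 5 (Follow-up): "Patients will be telephoned at 3 to 5 days by a study investigator to encourage treatment compliance and EOT visit follow-up". No measurement is scheduled. If symptoms worsen, "a return for clinical assessment may be recommended".
- EOT, day 7 to 10 (Follow-up): the patient is seen "in the enrolment centre and the area of infection will be measured".

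The day-30 contact comes after the endpoint and may be a telephone call. The primary outcome is the proportion with "greater than or equal to a 50% reduction in the maximal diameter of erythema from the area measured at enrolment", and Secondary outcomes defines failure as not reaching that reduction.

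**The concern.** Carrying a value forward is meant for endpoints measured repeatedly. Here the only scheduled earlier value is the baseline itself, so LVCF imputes a 0% reduction, which is a failure. It therefore acts as a missing-equals-failure rule without saying so. A patient who recovered and saw no reason to return is counted with those whose infection did not respond.

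Two things are at stake. First, failures added equally to both arms lower both success rates. They also raise the variance, because the rates move from 85% towards 50%, and that costs power. Second, if the true difference is also present among the missing patients, the added failures shrink the observed ITT difference. In a non-inferiority trial that is the anti-conservative direction, and it adds to the liberality of ITT that the protocol itself warns about.

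**Working it through.** **Inputs.** From Sample size, power and statistical methods: success 85% on dual therapy, margin Δ = 0.125, one-sided α = 0.025, power 90%, 172 per arm. From Patient randomisation: exactly 172 per arm are to be randomised. Assumed here, because the protocol gives no figure: a share m of 5%, 10% or 20% without an EOT diameter, equal in both arms and unrelated to outcome. Patients without an EOT value are taken to be outside the per-protocol set, which is otherwise all observed patients.

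**Step 1: reproduce the stated sample size.** n = (1.960 + 1.282)² × 2 × 0.85 × 0.15 / 0.125² = 10.507 × 0.255 / 0.015625 = 171.5, so 172 per arm. This matches. Power at 172 is 90.1%.

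**Step 2: effect of LVCF on the rates.** A true success rate p becomes p(1 − m). At m = 10%, 85% becomes 76.5% and 72.5% becomes 65.25%, so a true deficit of 12.5 points appears as 11.25.

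**Step 3: ITT error and power.** P(declare) = Φ[(Δ − d)/SE − 1.960], where d is the apparent deficit and SE = √[p₁(1 − p₁)/172 + p₂(1 − p₂)/172]. At m = 10%:

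- Type I error: d = 0.1125, SE = 0.0486. (0.125 − 0.1125)/0.0486 = 0.257, and Φ(0.257 − 1.960) = 0.044.
- Power (85% in both arms): d = 0, SE = 0.0457. 0.125/0.0457 = 2.734, and Φ(2.734 − 1.960) = 0.78.

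**Step 4: results.** The ITT columns are exact binomial enumeration with the unpooled Wald limit. The joint columns are simulation (400,000 runs). The last column uses the formula above with 172(1 − m) per arm.

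| Loss m | ITT error | Joint error | ITT power | Joint power | Power, observed patients only |
|---|---|---|---|---|---|
| 0% | 2.6% | 2.6% | 90.1% | 90.1% | 90.1% |
| 5% | 3.5% | 1.9% | 83.7% | 81.5% | 88.6% |
| 10% | 4.4% | 1.7% | 78.3% | 75.3% | 86.9% |
| 20% | 6.9% | 1.6% | 70.2% | 65.6% | 82.7% |

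**Step 5: separate the causes of the power loss.** Having fewer observed patients costs 90.1 − 88.6 = 1.5, 90.1 − 86.9 = 3.2 and 90.1 − 82.7 = 7.4 points, whatever the imputation. The further drop to joint power, 88.6 − 81.5 = 7.1, 86.9 − 75.3 = 11.6 and 82.7 − 65.6 = 17.1 points, is the part due to LVCF.

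**Step 6: unequal loss.** With 5% lost on dual therapy and 15% on monotherapy, and truly equal treatments, LVCF creates an apparent deficit of 0.85 × 0.95 − 0.85 × 0.85 = 8.5 points, and power is about 14%. With the losses reversed, ITT error at the margin is about 46%, while the joint rule holds it at about 2.5%.

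**The case against.** A reader might infer from the ITT error figures that the trial's false-positive rate is inflated. The documents do not support that for the scenario calculated. ITT cannot declare non-inferiority alone, and the joint rule keeps the rate below 2.5%. This objection stands, with one limit: the per-protocol analysis is unbiased only if loss is unrelated to outcome. Assuming for illustration that 40% of failures and 10% of cures go missing in both arms, per-protocol error is about 10.5%, ITT error 4.4% and joint error 2.8%.

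The ITT inflation itself depends on the lower monotherapy cure rate also holding among the missing. If the missing patients have the same underlying cure rate in both arms, the 12.5-point difference is preserved and ITT error stays at about 2.5 to 2.6% at 5% and 10% loss. If all of them are true failures, scoring them so is correct and power stays at 90%. This stands as a condition on the figures.

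Nor can one say that neither named method is usable. A mixed model of enrolment and EOT diameters is valid under missing at random, and an imputed EOT diameter can be converted to cure status. What remains is that the model adds little with a single post-baseline value and that the conversion is not stated. Likewise, not every missing patient must become a failure: an unscheduled return might yield a diameter, although no measurement is specified for it.

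Finally, the sentence is general, it also covers the quality-of-life scores, and a statistical analysis plan is to be agreed before unblinding. That would answer a complaint about missing detail. It does not answer this one, because the protocol names LVCF as acceptable and an analysis plan that follows it would inherit the problem.

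**Conclusion.** The point holds as a fault in a named method. With one scheduled post-enrolment diameter, LVCF normally amounts to missing-equals-failure for the primary endpoint. Under equal, outcome-independent loss of 5% to 20%, power for the trial's decision falls to about 82% to 66%, where analysing observed patients alone would keep about 89% to 83%. Nothing absorbs the loss, since the number randomised equals the required minimum. In the same scenario ITT becomes a weaker second check, because its difference is pulled towards zero. An inflated trial-level error rate is not shown: it is about 1.6 to 1.9% here. All sizes rest on assumed loss rates, on loss unrelated to outcome, and on a per-protocol set equal to the observed patients.

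**What to change.** In Data analysis, remove LVCF as an option for the primary endpoint and state one method. For the ITT analysis, multiply impute the missing EOT diameter (or cure status) within arm from baseline diameter and other recorded baseline variables such as Eron class and centre. Derive cure in each completed data set and pool the risk differences. Use post-baseline information only where it is actually recorded: the protocol does not say that the day 3 to 5 call captures clinical status, or that antibiotic changes are captured in patients who never return.

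Add a tipping-point analysis that lowers the imputed cure probability in the monotherapy arm in steps until non-inferiority is lost. Keep missing-as-failure only as a labelled sensitivity analysis.

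The cost is modest extra programming, and the main ITT analysis then relies on missing at random, which the tipping-point analysis probes. No extra visits are needed. Trial status says that enrolment has yet to begin, so the change can be made before any data exist. It does not restore the power lost through fewer observed patients.
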